## Abstract

Currently the mechanisms that lead an atherosclerotic plaque to become unstable and those that trigger the coagulative/thrombotic processes leading to acute coronary syndrome have yet to be clarified. It has been suggested a possible role of microRNAs in the physiopathology of the atherosclerotic process related to acute and chronic ischemic cardiomyopathy. However, no data exists on the correlation between microRNAs expression in coronary (upstream and downstream of the coronary lesion) and arterial (at the aortic root level) blood from patients with acute coronary syndromes (ACS) and chronic coronary syndromes (CCS) before and after angioplasty. The study’s primary objective is to assess miRnome analysis in coronary and arterial blood sampling in ACS and CCS patients before and after angioplasty. The secondary objective is to analyze interleukin-6 and soluble ST2 levels in the peripheral plasma samples before and after angioplasty. Ten patients with ACS and ten patients with CCS will be enrolled. Coronary stenosis treated with angioplasty will be located in the proximal segments of the three main vessels: the anterior interventricular artery, the circumflex artery, and the right coronary artery. The angioplasty procedure will be performed according to standard clinical practice. Before and after angioplasty, blood samples upstream and downstream of the coronary lesion will be taken, arterial sampling at the aortic root level will be performed, and peripheral venous blood will be collected. The expression of serum microRNAs will be analyzed by Next-generation sequencing. Quantitative analysis of pro- and anti-inflammatory molecules such as interleukin-6 and the soluble form of the soluble ST2 will be performed on various blood samples. This study is registered in ClinicalTrials.Gov on October 30, 2023 (ID NCT06103357).

## Introduction

Acute Myocardial Infarction (AMI) is the principal clinical presentation of coronary artery disease (CAD) [1]. Despite decades of studies of AMI pathophysiology, many aspects remain to be clarified. In particular, mechanisms that lead an atherosclerotic plaque to become unstable and those that trigger coagulative/thrombotic processes leading to acute coronary syndrome (ACS). ACS is a broad term for conditions such as Non-ST-Elevation Myocardial Infarction (NSTEMI), ST-elevation myocardial infarction (STEMI), and Unstable Angina [2]. The most accepted pathophysiological hypotheses maintain that AMI is related to plaque rupture or erosion of vulnerable plaque [3], and inflammation was hypothesized to play a role in this context [4,5]. Atherosclerotic plaque formation is an inflammatory process in the endothelial vessel associated with low-density lipoprotein retention (LDL) [6]. Some potential biomarkers from atherosclerotic plaques have been described [7].

miRNAs are small regulatory RNAs involved in different biological processes and pathologies and could be efficient biomarkers for diseases. The role of miRNAs in regulating different biological pathways involved in the development and progression of atherosclerosis has been found using preclinical models [8]. In humans, altered expression of several circulating miRNAs has been identified in the presence of stable atherosclerotic plaques [9]. Our group previously identified the circulating miRNAs involved in modulating the inflammatory state, the inflamma-miRs, and miRNAs associated with cardiomyocyte necrosis (miR-499) [10,11]. However, no published data exists on the correlation between microRNA expression in coronary, arterial, and peripheral venous blood from patients with acute (ACS) or chronic (CCS) coronary syndromes.

During ACS, the plaque becomes unstable, triggering biological processes that lead to partial or complete vessel thrombosis. Many of these mechanisms remain unclear and it has been shown that miRNAs are involved [12–15]. In this study we aim to investigate whether there are differences in the expression of miRNAs before and after the activation of an unstable plaque. Specifically, we aim to compare these findings with the miRNA profile in a stable plaque associated with CCS. In this way, this study will investigate if there is a different expression of miRNAs downstream of the unstable plaque, differing from the levels present before the plaque activation, which leads to the acute event.

It is known that some miRNAs are involved in cellular regeneration [16], thrombotic processes [17], and activating inflammatory pathways [11]. miRNome analysis from different blood samples of ACS and CCS patients could reveal the mechanisms involved in the pathogenesis of AMI and bring new input to clinical and therapeutic perspectives.

This study will enroll patients affected by ACS and CCS with clinical indications for coronary angiography, demonstrating the presence of significant coronary artery disease. Three types of samples will be collected, before and after angioplasty. From peripheral venous blood, samples upstream and downstream of the coronary lesion, and samples at the aortic root level.

Blood flow before the coronary lesion could reflect more systemic conditions, such as inflammatory status and endothelial dysfunction. Downstream regions of the coronary lesions are characterized by lower oxygenation and nutrient flow due to the restricted blood flow, which could alter the miRNAs profile. Changes in miRNA levels downstream of a coronary lesion may be due to unregulated secretion from injured/stressed cells.

This study aims to test the miRNome picture in the blood of subjects undergoing an angioplasty procedure according to standard clinical practice. The expression of circulating miRNAs will be analyzed by Next-generation sequencing (NGS). In addition to blood sampling, where possible, plaque fragments will be taken to highlight differences in the biomarkers examined, particularly the immune/inflammatory profile. In addition to miRNome analysis, this protocol will include the quantitative analysis of pro and anti-inflammatory molecules such as interleukin-6 (IL-6) [18,19] and the soluble form of the interleukin-33 receptor (sST2) [20–22]. IL-33/sST2 axis is involved in the modulation of the inflammatory response since sST2 exerts proinflammatory effects when secreted into the circulation. Previous studies demonstrated that elevation of serum sST2 levels was associated with poor prognosis not only in patients with heart failure (HF) but also with myocardial infarction (MI), hypothesizing that elevated serum sST2 level might be closely related to vulnerable plaque features [23]. Recently it was hypothesized that elevated serum sST2 levels might be closely related to vulnerable plaque features, serving as a simple biomarker for coronary plaque vulnerability [24].

## Methods

### Study design

This protocol (Version 1.0_15 December 2022) has been approved by the Ethics Committee of the IRCCS INRCA (reference ID: CE-INRCA-22032). This work describes a pilot observational study protocol. Ten patients with NSTEMI ACS and ten patients with SCC with clinical indication and favorable anatomy for coronary angioplasty at the Interventional Cardiology Unit, IRCCS INRCA, Ancona, Italy, will be enrolled in this study. Inclusion/exclusion criteria will be applied. Patients who meet the inclusion criteria and wish to participate in the trial must sign a written informed consent presented by a physician. A schematic representation of the study design is shown in (Fig 1).

**Fig 1 pone.0324467.g001:**
[figure not shown]
Schematic representation of the study design.

### Objectives

#### Primary objective.

To compare miRNome profile in coronary and arterial blood samples between ACS and CCS patients before and after angioplasty.

#### Secondary objective.

To compare levels of biomarkers of inflammation such as IL-6 and sST2 in plasma samples between ACS and CCS subjects before and after angioplasty.

### Inclusion/exclusion criteria

#### Inclusion criteria.

Age > 18 years;Signed written informed consent;Clinical indication for the percutaneous coronary intervention (PCI) procedure according to the European Society of Cardiology (ESC) Guidelines [25];Coronary stenosis treated with angioplasty must be located in the proximal segments of the three main vessels: the anterior interventricular artery, the circumflex artery, and the right coronary artery;The vessels must have a diameter of their mid-distal section ≥ 3 mm;For ACS group: patients with NSTEMI ACS and clinical indication with favorable anatomy for PCI;For CCS group: patients with clinically incipient CCS with stable angina (or significant anginal equivalents) and clinical indication with favorable anatomy for PCI.

#### Exclusion criteria.

Contraindications to anticoagulant/antiplatelet therapy;Extensive calcifications and/or tortuosity of the major epicardial segments;Evidence of thrombotic occupation;Patients with hemodynamic instability;Patients with EF (ejection fraction) < 35%;Patients with severe chronic renal failure (e-GFR < 30 mL/min).

### Patient screening and recruitment

During the screening phase, information on the of the subject’s health status (diagnosis, medical history, and pharmacological therapies), socio-demographic data will be taken, and anthropometric parameters will be measured. In addition, participants will undergo blood tests according to the profile described in Table 1. The patient’s clinical data will be collected during the care pathway through an electronic medical record. The trial is opened for patient enrollment and recruitment on 06 March 2023.

**Table 1 pone.0324467.t001:** Study schedule.

	Screening	ACS group		CCS group	
		Before angioplasty	After angioplasty	Before angioplasty	After angioplasty
Informed consent	X				
Recording demographic data	X				
Medical history	X				
Pharmacological therapy	X				
Anthropometric measurements	X				
Fool blood exam-FBE^1^	X				
Leukocytes formula^2^	X				
Renal function^3^	X				
Liver function^4^	X				
Lipid profile^5^	X				
Electrolytes^6^	X				
Fasting glucose	X				
C-reactive protein	X				
Erythrocyte sedimentation rate	X				
High-sensitivity cardiac troponin	X				
Uric acid	X				
Prothrombin time	X				
Interleukin-6	X	X	X	X	X
sST2^7^	X	X	X	X	X
miRNome		Blood samples upstream and downstream of the coronary lesion	Blood samples upstream and downstream of the coronary lesion	Arterial sampling at the aortic root level	Arterial sampling at the aortic root level

ACS = acute coronary syndrome; CCS = chronic coronary syndrome;

^1^White blood cells (WBCs), red blood cells (RBCs), hemoglobin, hematocrit, mean cell volume (MCV), mean corpuscular hemoglobin (MCH), mean corpuscular hemoglobin concentration (MCHC), red cell distribution width (RDW), platelets;

^2^Neutrophils, eosinophils, basophils, lymphocytes, monocytes;

^3^Creatinine; estimated glomerular filtration rate by CKD-EPI equation;

^4^Aspartate aminotransferase glutamic oxaloacetic transaminase (AST/GOT), alanine aminotransferase/ glutamic pyruvic transaminase (ALT/GPT);

^5^Total cholesterols, triglyceride, low-density cholesterol (LDL), and high-density cholesterol (HDL);

^6^Sodium, potassium, magnesium;

^7^Soluble form of the IL-33 receptor.

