### Coronary angiography/angioplasty procedure and conservation of plaque samples

Coronary stenosis treated with angioplasty needs to be located in the proximal segments of the three main vessels: the anterior interventricular artery, the circumflex artery, and the right coronary artery.

The coronary angiography will be performed with radial or femoral arterial access, using introducers and 6 or 7 F catheters, and with a Siemens Artis angiography system (Siemens Healthineers, Forchheim, Germany). Intracoronary ultrasonography (IVUS), which is routinely performed in hospital INRCA, Ancona, Italy, in case of complex angioplasties, will also be carried out using the Philips Core Mobile system, which will allow the evaluation of the plaque both with the grayscale and with the virtual histology. The angioplasty procedure will be performed according to standard clinical practice. Blood samples and, when possible, fragments of plaque/thrombus in proximity (< 10 mm, upstream and downstream) of the coronary lesion will be taken before and after angioplasty using the Pronto LP 5 F microcatheter (Teleflex Inc. USA). The distal protection system used to collect plaque fragments during the interventional procedure will be the Spider FX Embolic Protection System (Medtronic Europe). The system consists of a microcatheter with a guide wire at the end at which point a nitinol basket of variable size is fixed. At the beginning of the interventional procedure, it will be positioned distal to the lesion to be examined. The filter’s patency, will allow the collection of plaque fragments that may dislodge during the procedure without interfering with the blood supply to the vessel’s periphery. At the end of the procedure, the filter will be removed and the plaque fragments will be taken. The material collected in the basket of the Spider Fx device will be carefully removed from the filter, collected in Falcon-type test tubes, and frozen at -80° C for future analysis at the Hospital INRCA laboratory, Ancona, Italy. Samples at the aortic root level will be drawn using a JR4 Super Torque Plus 5 F diagnostic catheter (Cordis Inc. USA) and venous samples from peripheral blood.

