### Blood samples

Before and after angioplasty, the following blood samples will be taken:

Peripheral venous bloodUpstream and downstream of the coronary lesionArterial samples at the level of the aortic root

Blood samples will be centrifuged, plasma and serum samples will be aliquoted and frozen at -80°C until further analysis.

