### Outcomes

Difference in miRNome profile in blood samples upstream and downstream of the coronary lesion and arterial samples at the level of the aortic root between ACS and CCS subjects;Difference in pro- and anti-inflammatory molecules such as IL-6 and sST2 levels in peripheral bloods samples before and after angioplasty.

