### Statistical analysis

The expression values of circulating miRNAs and pro- and anti-inflammatory molecules in arterial and venous blood samples will be compared by paired measures tests before and after the interventional procedure. Furthermore, the levels of biomarkers between the two groups of patients (ACS and CCS) for the various types of sampling will be compared by tests for the comparison between independent samples. A value of p < 0.05 will be considered statistically significant.

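### The miRNome row of Table 1 gives the two patient groups different sampling sites, contradicting the primary objective, sample list, outcome and between-group tests

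*Protocol article*

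**What the plan says.** All references are to the Protocol article.

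- **Table 1 (Study schedule), miRNome row.** Both ACS columns read "Blood samples upstream and downstream of the coronary lesion". Both CCS columns read "Arterial sampling at the aortic root level". No site appears under both groups.
- **Primary objective.** "To compare miRNome profile in coronary and arterial blood samples between ACS and CCS patients before and after angioplasty".
- **Procedure section.** Blood from close to the lesion, on either side "of the coronary lesion will be taken before and after angioplasty using the Pronto LP 5 F microcatheter". Aortic-root samples are drawn with a separate diagnostic catheter. Neither statement is restricted to one group.
- **Blood samples.** "Before and after angioplasty, the following blood samples will be taken", followed by a single list for all patients: peripheral venous, upstream and downstream coronary, and aortic root. Plasma and serum are aliquoted and stored at -80°C. The Abstract gives the same sites, also without a split by group.
- **Outcomes.** The first outcome is the difference in miRNome in "blood samples upstream and downstream of the coronary lesion and arterial samples at the level of the aortic root between ACS and CCS subjects".
- **Statistical analysis.** Biomarker levels in the two groups "for the various types of sampling will be compared by tests for the comparison between independent samples".
- **Biomarkers analyses.** Next-generation sequencing is named as the method, but the section does not say which samples are sequenced.

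**The concern.** The primary question is whether ACS and CCS patients differ in miRNome at given sites. That needs at least one site measured in both groups, and the stated outcome needs three. Table 1, as printed, provides none: ACS patients contribute only coronary profiles and CCS patients only aortic-root profiles. Any difference between the groups would then also be a difference between coronary and aortic blood, and no model could tell the two apart.

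The Introduction also says that findings at the unstable plaque will be set against the profile at a stable plaque in CCS. Under Table 1 the CCS group has no coronary profile, so that comparator would be missing from the sequenced data.

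The conflict matters in practice because Table 1 is the only place that assigns miRNome samples by group and time. Someone deciding which aliquots to sequence could reasonably work from it. Enrolment opened on 6 March 2023, so some patients may already have been handled under one reading or the other.

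**Working it through.** The article gives no sample-size or power figure on this point to reproduce. The check is a count of profiles, followed by a test of whether the group effect can be estimated.

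**Inputs**
- Patients: 10 ACS and 10 CCS (Abstract; Study design).
- Time points: 2, before and after angioplasty.
- Sites in the primary outcome: 3, namely upstream, downstream and aortic root (Outcomes).
- Sites in Table 1: 2 for ACS (upstream, downstream) and 1 for CCS (aortic root).

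**Profiles, as patients × sites × times**
- Required by the outcome: 20 × 3 × 2 = 120.
- Scheduled in Table 1: ACS 10 × 2 × 2 = 40; CCS 10 × 1 × 2 = 20; total 40 + 20 = 60.
- Ratio: 60 / 120 = one half.

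**Patients available for each between-group test (the same at each time point)**

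| Site | Table 1: ACS vs CCS | Sample list: ACS vs CCS |
|---|---|---|
| Upstream | 10 vs 0 | 10 vs 10 |
| Downstream | 10 vs 0 | 10 vs 10 |
| Aortic root | 0 vs 10 | 10 vs 10 |

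The outcome implies 3 sites × 2 times = 6 between-group contrasts. Table 1 supports 0 of 6, and the sample list supports 6 of 6.

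**Estimability**

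Take a model with an intercept, group (1 = ACS), indicators for upstream and downstream (aortic root as reference), time, and group × time: six columns.
- Under Table 1, every ACS profile is upstream or downstream and every CCS profile is aortic root, so group = upstream + downstream in every row. The 60-row matrix has rank 5 of 6, and the group effect is not estimable.
- Under the sample list applied to both groups, the 120-row matrix has rank 6 of 6, and the group effect is estimable.

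**What Table 1 would still allow**

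Before-versus-after comparisons within each group, and upstream versus downstream within ACS. Neither is the ACS-CCS comparison in the primary objective.

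**The case against.** The strongest reply is that this is one outlying table row. The Abstract, primary objective, procedure text, sample list, outcome and analysis all describe the sites without dividing them by group. Nor is Table 1 an exhaustive sampling plan: it has no row for peripheral venous draws as such, plaque fragments or intravascular ultrasound, and it names no sampling site for IL-6 or sST2. The counts above measure what a literal reading of the row would produce; they are not evidence that anyone followed it.

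Most of this stands. A reader might infer from Table 1 that the investigators chose a design in which group and site are confounded. The documents do not support that, because every other statement points the other way. A reader might also infer that the primary outcome is beyond recovery. That does not follow either: if blood was collected according to the sample list and only the sequencing followed Table 1, the omitted aliquots are in the freezer and can still be analysed.

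The reply does not make the conflict harmless. The sample list says what blood is drawn, not what is sequenced, and the section on biomarker analyses does not settle it. All four cells of the miRNome row are filled and line up with their headings, so a fault in reading the table from the PDF is unlikely.

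A further possible complaint is that Table 1 schedules no venous miRNome although the Statistical analysis section refers to venous samples. That sentence covers miRNAs and inflammatory molecules together, in arterial and venous blood. The objective and outcome place the miRNome at coronary and aortic sites only. This is an ambiguity, not an error.

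**Conclusion.** The point holds as an internal contradiction on the primary outcome, probably a mistake in the table. If sequencing followed Table 1 literally, 60 of 120 profiles would be produced, 0 of 6 site-by-time ACS-CCS contrasts could be formed, and the group effect would be fully aliased with site.

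This rests on two conditions:
- **Sequencing followed Table 1.** The article does not show that any patient was handled this way.
- **For the loss to be permanent, collection also followed Table 1.** If the sample list governed collection, the gap can be closed from stored aliquots.

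The contradiction should be corrected before the ACS-CCS comparison is run. It concerns the main question of the study, and samples taken around the procedure cannot be repeated if they were missed.

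**What to change.** 1. Reconcile the miRNome row of Table 1 with the primary objective, procedure section, sample list, outcome and between-group tests, so that upstream, downstream and aortic-root samples are listed before and after angioplasty for both groups.
2. For patients already enrolled, confirm which sites were collected and which were sequenced. Sequence stored aliquots where they exist.
3. Limit between-group tests to sites available in both groups, and declare any site-by-time combination that is missing.
4. As a minor clarification, state whether peripheral venous samples are sequenced for miRNA.

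The cost is a table correction, a short protocol clarification and a check of sample records. The 120 profiles are already implied by the stated outcome, so no new design decision is needed. If sequencing has so far followed Table 1, completing it means up to 120 − 60 = 60 further profiles from stored material.

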### Coronary angiography/angioplasty procedure and conservation of plaque samples

Coronary stenosis treated with angioplasty needs to be located in the proximal segments of the three main vessels: the anterior interventricular artery, the circumflex artery, and the right coronary artery.

The coronary angiography will be performed with radial or femoral arterial access, using introducers and 6 or 7 F catheters, and with a Siemens Artis angiography system (Siemens Healthineers, Forchheim, Germany). Intracoronary ultrasonography (IVUS), which is routinely performed in hospital INRCA, Ancona, Italy, in case of complex angioplasties, will also be carried out using the Philips Core Mobile system, which will allow the evaluation of the plaque both with the grayscale and with the virtual histology. The angioplasty procedure will be performed according to standard clinical practice. Blood samples and, when possible, fragments of plaque/thrombus in proximity (< 10 mm, upstream and downstream) of the coronary lesion will be taken before and after angioplasty using the Pronto LP 5 F microcatheter (Teleflex Inc. USA). The distal protection system used to collect plaque fragments during the interventional procedure will be the Spider FX Embolic Protection System (Medtronic Europe). The system consists of a microcatheter with a guide wire at the end at which point a nitinol basket of variable size is fixed. At the beginning of the interventional procedure, it will be positioned distal to the lesion to be examined. The filter’s patency, will allow the collection of plaque fragments that may dislodge during the procedure without interfering with the blood supply to the vessel’s periphery. At the end of the procedure, the filter will be removed and the plaque fragments will be taken. The material collected in the basket of the Spider Fx device will be carefully removed from the filter, collected in Falcon-type test tubes, and frozen at -80° C for future analysis at the Hospital INRCA laboratory, Ancona, Italy. Samples at the aortic root level will be drawn using a JR4 Super Torque Plus 5 F diagnostic catheter (Cordis Inc. USA) and venous samples from peripheral blood.

